**Methods/design:**

This is a sham-controlled, three-armed randomized clinical trial. A total of 165 participants with BMI between 25 and 39.99 and aged between 18 and 60 who meet the inclusion and exclusion criteria will be randomized into [1] electroacupuncture plus mindfulness meditation group, [2] sham electroacupuncture plus mindfulness meditation group, and [3] electroacupuncture only group. The total duration of this study will be 22 weeks, which consists of a 2-week run-in period, a 12-week intervention period, and an 8-week follow-up period. Participants will receive 12 weekly treatments during the intervention period. Primary outcomes will include body mass index, waist and hip ratio, and body composition. Secondary outcomes will be measured by the Weight-Related Symptom Measure, Obesity and Weight Loss Quality of Life, the Power of Food Scale, and the Chinese medicine differential diagnosis questionnaire. Outcomes will be assessed at the baseline, and endpoints of the 3rd, 6th, 9th, 12th, 14th, 16th, and 20th week.

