## Outcome measurements

### Primary outcome

#### Weight and body mass index (BMI)

The primary focus of the outcome measurements is on the effectiveness of the interventions in reducing the severity of overweight or obesity. It includes the change in body weight in Kg and BMI. BMI is a commonly used tool for assessing the risk of overweight and obesity for individuals [1]. It is calculated using the following equation:$$\mathrm{BMI}=\frac{\mathrm{Mass}\ \left(\mathrm{Kg}\right)}{\left(\mathrm{Height}\ \left(\mathrm{m}\right)\right){\mathrm{H}}^2}$$

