#### Body composition

Body composition involves measuring the body fat percentage (Fat %) by using the Dual Energy X-ray Absorptiometry (DXA) scan. DXA is a type of medical imaging technology which uses low dose radiation for the whole-body scan to provide the measurement of Fat %. The scanning will be performed by qualified operators.

The measurements of body composition will be taken from the baseline, the 12th and 20th-week visit.

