### Statistical analysis

Statistical analysis will be performed using Statistical Package for Social Science (SPSS) at the Discipline of Chinese Medicine, School of Health and Biomedical Science, RMIT University, at the end of the trial. Given the short duration of the trial, no interim analysis will be conducted. Intention-to-treat (ITT) analysis will be used for participants who are randomized and participated for at least one treatment session. The Worst-Case Scenario method will be employed to deal with the missing data. Continuous variables will be summarised using the mean, standard deviation, and 95% confidence intervals, while quantitative variables will be presented using the maximum and minimum values. Baseline data and clinical characteristics will be used to compare the baseline data between intervention groups. Analysis of covariance (ANCOVA) will be performed on BMI and WHR to determine the mean difference between groups at the end of treatment and follow-up period. All comparisons will be two-tailed, and *p* values < 0.05 will be considered statistically significant.

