## Discussion

Overweight and obesity have reached an epidemic level across the world over the past decades [1]. More effective weight management strategies are urgently needed to reduce the prevalence and impacts on our society. Due to the multifactorial cause of overweight and obesity, interventions that only target one single factor may not achieve a satisfying weight management outcome [60–62].

Evidence has shown that acupuncture is effective in weight management when it is being used alone or combined with other weight loss interviews to enhance weight loss outcomes [32, 38, 40]. EA is a variant of acupuncture with a replicable mode of stimulation that enables consistent stimulation throughout treatment sessions [21]. Additionally, other evidence has suggested that mindfulness meditation may be added to weight loss programs to enhance the treatment results [52]. Furthermore, the clinical practice guidelines for the management of overweight and obesity in adults, adolescents and children in Australia suggest that psychological component can be added to weight loss programs to increase the likelihood of success [11]. To our best knowledge, this is the first trial protocol evaluating the effect and safety of EA combined with mindfulness meditation for weight management.

The aim of this RCT is to evaluate the add-on effect of EA and MM on weight loss. In terms of group design, the add-on effect of EA will be evaluated by comparing the EAM group and SAM group. The add-on effect of MM will be assessed by comparing the EAM group and the EAO group. This design has put a limitation on this trial in which we cannot blind the participants for the EAO group who will not be participating in the MM component. Participants in the EAM and SAM groups will be blinded by sham electroacupuncture treatment. The SA method was designed as penetrating insertion to a non-acupuncture point, all acupuncturists will receive training on needling to the predefined non-acupuncture points to ensure consistency of point location for the SAM group. The wire of the electro-stimulator will be modified to stop the current being flow to the body; this ensures that the SAM group participants receive no electro-stimulations at all. Participants will be told that the intensity of stimulation is predefined, and therefore they may or may not be able to feel for the stimulation.

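### BMI and WHR are tested at two times and for two contrasts, each at an unadjusted 0.05, while the sample size plans 5% for one BMI comparison and no primary test is named

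*Protocol article*

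**What the plan says.** **Primary outcomes.** The Abstract lists three without ranking them: "Primary outcomes will include body mass index, waist and hip ratio, and body composition". Under the Primary outcome heading the article adds body weight: "It includes the change in body weight in Kg and BMI". WHR and DXA body fat percentage have their own subsections under the same heading. For the DXA measure, "The measurements of body composition will be taken from the baseline, the 12th and 20th-week visit".

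**Contrasts.** Background gives two aims of equal standing: what MM adds to EA, and what EA adds to MM. The Discussion ties each aim to a comparison. For the first, "the add-on effect of EA will be evaluated by comparing the EAM group and SAM group"; EAM vs EAO then serves for MM. The Group design section assigns the same two comparisons the other way round.

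**Analysis.** ANCOVA is named for two outcomes only: it "will be performed on BMI and WHR to determine the mean difference between groups at the end of treatment and follow-up period". The decision rule is "All comparisons will be two-tailed, and" p "values < 0.05 will be considered statistically significant". There is no ordering and no division of alpha.

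**Sample size.** This section uses one outcome (BMI), one comparison (acupuncture vs sham) and one occasion (after treatment). The effect size is 0.56, with 80% power and 5% significance, giving 55 per group and 165 in total.

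**The concern.** The 5% used to size the trial belongs to one test. The analysis section spends 5% on each of several tests of outcomes that all carry primary status, and nothing says which of them decides the trial. The Discussion considers what would follow from a positive result without defining one. As written, a significant WHR difference at week 20 for EAM vs EAO could be presented as a primary finding on the same footing as BMI at week 12 against sham. The type I error attached to a claim of success would then be well above the level in the Sample size section, and the choice of headline result could be made after seeing the data.

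**Working it through.** **1. The plan's own figure.** With d = 0.56, two-sided 0.05 and 80% power, n per group = 2(1.960 + 0.842)²/0.56² = 50.1, so 51. The t-test gives 51.03, so 52. The stated 55 is slightly larger than one unadjusted comparison needs, and power at 55 per group is 82.9% (t-test). The planned size therefore covers one comparison at the full 5%, with no room for a split alpha.

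**2. Counting the tests.** Two outcomes with a named test (BMI, WHR) × two times (end of treatment, week 12; end of follow-up, week 20) × two contrasts = 8. If DXA fat percentage were tested in the same way, the count would be 3 × 2 × 2 = 12.

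**3. Upper reference.** If the tests were independent, 1 − 0.95⁸ = 33.7%. They are not independent, so correlations are needed.

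**4. Correlations.**
- Between the two contrasts: 0.5. This follows from the shared EAM arm and the 1:1:1 allocation.
- Between outcomes: assumed 0.3 to 0.7.
- Between week 12 and week 20: assumed 0.6 to 0.9.

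The documents do not give the last two.

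**5. Simulation under the global null.** Multivariate normal test statistics, 400,000 draws per setting. The event is at least one significant result at two-sided 0.05.

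| Reading of the plan | Chance of at least one false positive |
|---|---|
| BMI and WHR, two times, two contrasts (8 pairwise tests) | 20-28% |
| BMI and WHR, two times, within one contrast (4 tests) | 12-16% |
| Four three-group omnibus ANCOVAs | 12-17% |
| Omnibus first, contrasts read only if it is significant | 10-14% |
| BMI alone, one time, two contrasts | 9% |
| Fat percentage also tested under the same rule (12 tests) | 26-38% |

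In each range the low end belongs to the strongest assumed correlations (0.7 and 0.9) and the high end to the weakest (0.3 and 0.6). If correlations as low as zero between outcomes and between times are allowed, the eight-test figure reaches about 32%.

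**6. Power under possible repairs** (55 per group, d = 0.56, t-test). At 0.05: 82.9%. At 0.025: 74.6%. Bonferroni over eight tests, 0.05/8 = 0.00625: 56%.

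**The case against.** **This could be left to the analysis plan.** The article condenses a fuller protocol, and multiplicity procedures often sit in a statistical analysis plan that is not shown. That would answer a complaint about silence. Here the article states a rule, an unadjusted 0.05 for every comparison, next to several unranked primary outcomes. An analysis plan with a hierarchy would have to override that sentence.

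**Eight tests is a reading.** The text does not say whether the ANCOVAs are pairwise or three-group. This stands, and the omnibus readings lower the figure to 10-17%.

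**The two contrasts answer separate questions.** Controlling error per question is a common and defensible position, and Background does state two aims. It removes one source of inflation but leaves two outcomes at two times, 12-16% per contrast.

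**The figures need a rule that any significant result makes the trial positive.** The documents state no such rule, nor any other, so the figures are conditional on it. The 5% in the Sample size section is likewise an input to one calculation and not a promise about the whole trial.

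**A stronger reading to avoid.** From the list of three or four primary outcomes a reader might infer that all are tested at 0.05, with an error rate up to 38%. The documents do not support this. The analysis section names a test for BMI and WHR only, and none for body weight or fat percentage. The 26-38% range applies only if fat percentage is tested under the same rule.

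**Conclusion.** The concern holds for the tests the protocol names. At least two unranked primary outcomes, at two times and for two contrasts, are each judged at an unadjusted 0.05, while the trial is sized on one BMI comparison at 5%. The chance of at least one false positive is about 20-28% over eight pairwise tests, 12-16% within a single contrast, and 10-17% under the omnibus readings. These ranges rest on the assumed correlations and on counting any significant result as success. The exact size is therefore uncertain. That it exceeds 5% is not, since each of these readings does. The sample size points to BMI against sham as the planning comparison, but no section declares it the primary hypothesis. This should be corrected before the data are unblinded.

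**What to change.** 1. Name BMI at week 12 as the single primary endpoint, since the sample size rests on BMI after treatment.
2. Move body weight, WHR, fat percentage and all week 20 comparisons to secondary status, reported with confidence intervals and no confirmatory claim.
3. Make the Abstract, the three subsections under Primary outcome (weight and BMI, WHR, body composition) and the Statistical analysis section agree on this.
4. Reconcile Group design with the Discussion on which contrast measures which add-on effect. Ordered hypotheses cannot be written until this is settled.
5. State how the two contrasts share the 5%. Several choices are sound:
   - Fixed sequence, EAM vs SAM first at 0.05, then EAM vs EAO at 0.05 only if the first is significant. Power for the first contrast stays at 83%. The price is that nothing can be claimed for MM if the first test fails, although Background gives the two aims equal standing.
   - Holm across the two contrasts. Neither aim depends on the other, and power is about 75% per contrast at the 0.025 step.
   - Two separate questions at 0.05 each, if that is the intention. Say so, and state the joint error of about 9%.

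The cost is wording in the protocol and analysis plan. The Trial status section reports recruitment in progress and no interim analysis is planned, so the change can be made without knowledge of results. Leaving it to a blanket correction later would cost more: Bonferroni over the eight tests leaves 56% power.

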## Discussion

Overweight and obesity have reached an epidemic level across the world over the past decades [1]. More effective weight management strategies are urgently needed to reduce the prevalence and impacts on our society. Due to the multifactorial cause of overweight and obesity, interventions that only target one single factor may not achieve a satisfying weight management outcome [60–62].

Evidence has shown that acupuncture is effective in weight management when it is being used alone or combined with other weight loss interviews to enhance weight loss outcomes [32, 38, 40]. EA is a variant of acupuncture with a replicable mode of stimulation that enables consistent stimulation throughout treatment sessions [21]. Additionally, other evidence has suggested that mindfulness meditation may be added to weight loss programs to enhance the treatment results [52]. Furthermore, the clinical practice guidelines for the management of overweight and obesity in adults, adolescents and children in Australia suggest that psychological component can be added to weight loss programs to increase the likelihood of success [11]. To our best knowledge, this is the first trial protocol evaluating the effect and safety of EA combined with mindfulness meditation for weight management.

The aim of this RCT is to evaluate the add-on effect of EA and MM on weight loss. In terms of group design, the add-on effect of EA will be evaluated by comparing the EAM group and SAM group. The add-on effect of MM will be assessed by comparing the EAM group and the EAO group. This design has put a limitation on this trial in which we cannot blind the participants for the EAO group who will not be participating in the MM component. Participants in the EAM and SAM groups will be blinded by sham electroacupuncture treatment. The SA method was designed as penetrating insertion to a non-acupuncture point, all acupuncturists will receive training on needling to the predefined non-acupuncture points to ensure consistency of point location for the SAM group. The wire of the electro-stimulator will be modified to stop the current being flow to the body; this ensures that the SAM group participants receive no electro-stimulations at all. Participants will be told that the intensity of stimulation is predefined, and therefore they may or may not be able to feel for the stimulation.

Participants in EAM and SAM groups are required to practice MM daily and record their practice in a log book. The pre-recorded MM instructions will increase the flexibility for participants to practice MM at their preferable time.

Both objective and subjective outcome measurements will be evaluated in this trial. The current management of overweight and obesity includes lifestyle changes, pharmacotherapies and surgeries [63], and it is necessary to isolate the effect of these approaches to impact the study results. Therefore, participants will be asked not to undergo bariatric surgery or consume weight loss medications and continue their usual diet and physical activities. As a result, we can ensure that the change in the treatment outcome was attributed to the effect of the allocation study group. Although BMI is the major tool for assessing weight status [1], body fat composition will also be evaluated because it is necessary to investigate whether the reduction in BMI is due to the loss of body fat, muscle mass or bone density [64, 65]. Moreover, WHR is a commonly used tool for assessing abdominal obesity, linked closely to cardiovascular disease risk [66]. The idea of addressing overweight and obesity is to reduce the risk for other comorbidities like cardiovascular diseases [67]. Therefore, WHR will also be assessed to evaluate the effect of this combined intervention on abdominal obesity [68].

The WRSM, OWL-QoL, and Power of Food Scale were used to assess the psychological impact on overweight and obesity [69, 70]. If the result of this RCT is found positive, it will provide a novel cost-effect multicomponent weight management approach. It is anticipated that this approach may improve both physical and psychological outcomes for overweight and obese individuals.

Finally, this rigorously designed clinical trial protocol was developed by following the SPIRIT [54], CONSORT [56], and STRICTA [55] guidelines to minimize the risk of bias and the quality assurance for the combined intervention. If successful, this proposed protocol may provide a safe and cost-effective multidisciplinary approach for weight management.

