Previous systematic reviews have investigated the effect of acupuncture on improving weight loss in obese people [32, 36–45]. Two systematic reviews suggested that acupuncture can have a positive effect on waist circumference (WC) and hip circumference (HC), reducing the WC by 2.02cm (95%CI 0.21 to 3.83, *p*=0.03) and WC by 2.74cm (95%CI 1.21 to 4.27, *p*=0.0004) [44, 45]. Kim, Trinh [24] reported that acupuncture combined with exercise is more effective than e exercise alone in reducing BMI (Hedges’ *g* = 1.104, 95%CI 0.531 to 1.678) [10]. Chen et al. [46] and our previous research suggested that the mechanism of acupuncture for weight loss may be due to reducing excessive appetite and increasing metabolism [17, 20]. A systematic review on RCT of acupuncture for obesity suggested that acupuncture may lower serum leptin levels in obese adults [47].

Even though there is increasing evidence supporting the use of acupuncture for overweight and obesity [21], the current Australian clinical guidelines for obesity do not include acupuncture as a modality for treatment. Therefore, further investigations are needed to provide more evidence to assist clinical decisions.

Mindfulness meditation (MM) is a psychological approach with increasing popularity for weight management [48]. The term mindfulness is a concept that originated from Buddhist traditions. Mindfulness is defined as the awareness of paying attention to the current moment without judgment to the thought [49]. It has been further defined that mindfulness also involves in sustaining attention through self-regulation [50] and that the current moment should be experienced with an acceptance attitude [51].

A recent systematic review suggested that MM can be effective in improving eating behaviour such as emotional eating and binge eating and can be used in conjunction with other interventions for weight loss treatment [48]. Studies have found that better weight loss outcomes and eating behaviours have been achieved by adding MM to a standard behaviour weight loss program [48, 52].

There is evidence supporting that EA can enhance the outcome of diet and exercise for weight loss [37, 38], and MM can enhance the weight management outcome by improving eating behaviour [48]. However, the combination of EA and MM has never been investigated.

This clinical trial aims to clinically evaluate the add-on effect of MM to EA and vice versa for people with overweight or obesity.

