### Group design

This is a three-arm clinical trial, which consists of the EA plus MM group (EAM), SEA plus MM group (SAM) and EA only group (EAO). Participants will be asked to continue with their usual diet and exercise, and refrain from participating in any weight loss program or consuming any weight loss supplements/medications, otherwise will be considered as a dropout during the study. The description of each group is listed below (Table 2):

**Table 2 Tab2:** Group description

Group	Description
Electroacupuncture + MM (EAM)	This group consists of a combination of EA and mindfulness meditation interventions. Participants will be given the abovementioned EA treatment. They will then be prompted to follow the 10 min pre-recorded MM instruction. They will be instructed to practice MM daily.
Sham electroacupuncture + MM (SAM)	This group consists of a combination of EA and mindfulness meditation interventions. Participants will be given the abovementioned sham EA treatment. They will then be prompted to follow the 10 min pre-recorded MM instruction. They will be instructed to practice MM daily.
Electroacupuncture only (EAO)	This group consists of the abovementioned electroacupuncture treatment only.

*Abbreviations*: *MM* Mindfulness meditation, *EA* Electro-acupuncture

The add-on effect of MM to EA comparing the treatment group (EAM) with the control group (SAM). On the other hand, to assess the add-on effect of electroacupuncture on mindfulness meditation, the treatment group (EAM) will be compared with the control group (EAO).

Participants will confirm their next appointment during their visits, and a message will be sent to the participants to remind and confirm their weekly visits.

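### EAM versus EAO differs in blinding to electroacupuncture as well as in meditation, so it gives an open-label effect of adding the MM package, not an isolated MM effect

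*Protocol article*

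**What the plan says.** The last paragraph of the Background sets two parallel objectives: "This clinical trial aims to clinically evaluate the add-on effect of MM to EA and vice versa for people with overweight or obesity". Group design and Table 2 define the three arms. EAM gets real electroacupuncture (EA) and mindfulness meditation (MM), SAM gets sham EA and MM, and for EAO the table says "This group consists of the abovementioned electroacupuncture treatment only". No arm gives sham EA without MM.

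The Discussion links arms to objectives. For meditation it says "The add-on effect of MM will be assessed by comparing the EAM group and the EAO group", and it gives EAM versus SAM as the contrast for the EA add-on effect. On blinding it says "Participants in the EAM and SAM groups will be blinded by sham electroacupuncture treatment" and states this limitation: "This design has put a limitation on this trial in which we cannot blind the participants for the EAO group who will not be participating" (meditation is meant). It adds that participants are told they may or may not feel the stimulation.

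Group design attaches the two effects the other way round: the MM add-on effect to EAM versus SAM, and the EA add-on effect to EAM versus EAO.

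**The concern.** To read EAM versus EAO as the effect of MM, the EA background should be the same in both arms. It is physically the same, but it is received under different blinding. EAM participants are meant not to know whether their EA is real. EAO participants are outside that blinding, because sham never occurs without MM.

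The stated limitation reads like the ordinary one that meditation cannot be hidden. It does not say that the absence of MM may also reveal the EA as real, nor that this bears on one of the trial's two objectives. If the text stays as it is, a positive EAM versus EAO result could be reported as an effect of MM itself, and a null one as evidence that MM adds nothing. Neither follows. BMI, waist-hip ratio and DXA fat percentage are measured, but weight over 12 weeks can respond to what participants do, and the symptom, quality-of-life and Power of Food questionnaires are self-reported.

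**Working it through.** **1. What each contrast holds equal** (Group design, Table 2, Mindfulness meditation, Discussion)

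| | EAM vs SAM | EAM vs EAO |
|---|---|---|
| EA | real vs sham | real vs real |
| MM package | both | EAM only |
| Blinded to real vs sham EA | both | EAM only |

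The first contrast differs by design in one row. The second differs in two.

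**2. Why the absence of MM is informative.** Under the 1:1:1 allocation (Randomization):

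- Chance that EA is real, given MM: (1/3) / (1/3 + 1/3) = 1/2.
- Chance that EA is real, given no MM: (1/3) / (1/3) = 1.

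These are allocation proportions, not measured beliefs. They become beliefs only for participants who know how the arms are made up. The Exclusion criteria require everyone to be willing to have acupuncture and to practise meditation, so EAO participants can see that they have no MM. Whether they also know that sham goes only with MM is not shown.

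**3. The plan's own figure.** Sample size gives an effect size of 0.56, 80% power, 5% significance and 55 per group; Statistical analysis says two-tailed.

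- n per group = 2 × (1.960 + 0.842)² / 0.56² = 50.1, so 51; the t-test version gives 52.
- The stated 55 is therefore 3 to 4 above what its inputs give. An unstated 5% dropout allowance would produce it (52 / 0.95 = 54.7, so 55).
- Power at 55 per group: standard error = √(2/55) = 0.191 SD; 0.56 / 0.191 = 2.94; Φ(2.94 − 1.96) = 83.6% (82.9% by t-test).

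The present point does not depend on this figure.

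**4. Scale, by assumption only.** Let b be a net shift in SD between EAM and EAO that comes from the blinding difference. The document gives no value for b. With 55 per arm and a two-sided 5% test, the rejection rate for a shift d is Φ(d/0.191 − 1.96) + Φ(−d/0.191 − 1.96).

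| Assumed b | Rejection rate, no true MM effect (d = b) | Power, true effect 0.56, b against EAM | Power, b in favour of EAM |
|---|---|---|---|
| 0 | 5.0% | 83.6% | 83.6% |
| 0.1 | 8.2% | 67.4% | 93.3% |
| 0.2 | 18.2% | 47.1% | 97.9% |
| 0.3 | 35.0% | 27.6% | 99.5% |

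The 0.56 comes from a comparison of acupuncture with sham, so the power columns show sensitivity and do not predict anything about MM.

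**5. Which contrast answers which question.** EAM and SAM share MM and differ in EA, so they inform on EA. EAM and EAO share EA and differ in MM, so they inform on MM. The pairing in the Discussion fits the arm contents; the one in Group design does not.

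**The case against.** The strongest reply is that the protocol has already disclosed this. Straight after naming EAM versus EAO as the MM contrast, the Discussion calls the unblinded EAO arm a limitation, and it describes sham blinding for EAM and SAM only. That stands: nothing is hidden. What is missing is the step from the limitation to the objective, which stays unqualified.

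Four stronger readings are tempting, and the document does not support them.

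- *EAM participants are half sure and EAO participants certain that their EA is real.* The consent form (Additional file 2) is not shown, and Data management says group information is given on trial completion. Only the possibility of inference is supported.
- *The extra session time, booklet, home practice and log book are unmatched confounders.* The Mindfulness meditation section describes them as the intervention. They belong to the package being added, and adding a package without an attention control is a common choice.
- *The protocol claims to have isolated MM when it writes "we can ensure that the change in the treatment outcome was attributed to the effect of the allocation study group".* That sentence follows from barring surgery and weight-loss medication and keeping usual diet and activity. It is about co-interventions, though worded too broadly.
- *The contrast is biased by a known amount or in a known direction.* Certainty about EA could raise expectation in EAO, and missing out on MM could disappoint. The net could be zero.

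**Conclusion.** The point holds as one of interpretation. EAM versus EAO is an open-label estimate of adding the MM package to EA, in arms that also differ in blinding to EA. It is neither sham-controlled nor an isolated MM effect, and the two add-on contrasts are not of the same kind. It remains a usable pragmatic comparison; a reader might infer that it is invalid, but nothing in the document shows that. EAM versus SAM is unaffected.

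The conclusion rests on the arm structure and the protocol's own blinding statements. That EAO participants may infer real EA is an inference, since the participant information is not shown. No size can be given for the bias; the figures above only show that an assumed shift of 0.1 to 0.2 SD would matter at 55 per arm.

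**What to change.** 1. In the Background aim, Group design and the Discussion, describe EAM versus EAO as the open-label effect of adding the MM package to EA, and state that only EAM versus SAM is sham-controlled.
2. Extend the limitation in the Discussion: the absence of MM may also reveal that EA is real, so neither a positive nor a null EAM versus EAO result will be attributed to MM alone.
3. Limit the attribution sentence in the Discussion to co-interventions.
4. Reconcile Group design with the Discussion on which contrast gives which add-on effect.

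These are wording changes, with no added patients, arms or procedures and no change to participant information. The price is a narrower conclusion for the MM contrast.
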